#### Primary outcomes

The primary outcome is the effectiveness of the intervention in reducing dry mouth complaints in patients with a life-limiting condition or frailty. This is measured by the percentage responders at week 4, for which a clinically relevant response is defined as at least a 2-point reduction on the 11-point numeric rating scale (NRS). The NRS is a frequently used instrument in both clinical practice and research settings to score symptom severity, such as for pain, nausea and sleep [31]. The NRS for dry mouth ranges from 0 = no dry mouth symptoms to 10 = worst possible dry mouth symptoms [1, 7].

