#### Secondary outcomes

Secondary outcomes include effect durability, (mouth-related) quality of life, patient-reported functional status, global perceived effect by participants, cost-effectiveness, adherence and side-effects. The specific research instruments per outcome used are detailed in Table 2.

Effect durability is measured by the percentage responders at week 8 and 12, as well as by changes in mean NRS dry mouth scores in the intervention versus the control group at all time-points. Effectiveness as perceived by the patient is measured by a 7-point scale (the Global Perceived Effect, GPE) [37] rating how much the patients’ condition has improved or deteriorated since the start of the study in both the control and intervention group. The global perceived effect is measured using a 7-point scale, rating how much the patients’ condition has improved or deteriorated since the start of the study for both the control and intervention group.

Changes in mouth-related quality of life is examined at all time-points between groups using two different validated questionnaires: the Geriatric Oral Health Assessment Index (GOHAI-NL) [33] and the shortened Summated Xerostomia Inventory (sXI-D) [32]. The GOHAI-NL consists of 12 oral health related items and three categories: physical function, psychosocial function and pain/discomfort. The sXI-D consists of 5 items, addressing dry mouth in general and consequences of dry mouth, such as difficulty eating and swallowing. In addition, functional status and overall quality of life are measured by a validated patient-reported functional status scale (from 0 = normal with no limitations to 4 = bed ridden, rarely out of bed) [37] and the EuroQol 5 Dimensions 5 Levels (EQ-5D-5L) questionnaire [34] respectively. The latter will also be used for the cost-effectiveness analysis and assesses quality of life in five dimensions: mobility, self-care, usual activities, pain/discomfort and anxiety/depression. The EQ-5D-5L is complemented by the iMTA (Institute for Medical Technology Assessment) Medical Consumption Questionnaire (iMCQ) for the cost-effectiveness analysis [38]. The iMCQ measures medical consumption, including medical and paramedical treatments or services, in- and outpatient care and medication.

Lastly, in the pilocarpine study the adherence and side-effects from either the pilocarpine or the placebo are measured by using short-form questionnaires.

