#### MEP study

For this study, we expect the intervention group (patients who follow the MEP) to have at least 25% more responders (patients with clinically relevant less dry mouth at 4 weeks) than in the control group (patients who receive CAU). To test the null hypothesis (expected difference in responders at 4 weeks of 25%) with a power of 0.8, an alpha of 0.05 and an intra cluster coefficient of 0.10, we will need to include 181 patients which is obtained in 12 clusters (six hospitals and six nursing home clusters). Taking into account a 20% dropout rate at 4 weeks due to the frailty of our study population, 228 patients are needed. Each participating center is therefore expected to include 19 patients.

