### Data analysis

#### Analysis of effect evaluation

All analyses will be carried out using statistical software that supports multi-level mixed model analyses, including the latest version of IMB SPSS Statistics. Demographic and baseline disease characteristic data will be summarized for each treatment group by presenting descriptive statistics. For continuous variables, we will use the mean and standard deviation (SD) in case of a normal distribution, or median and first and third quartile in case of skewed distribution. In case of missing data, we will use stochastic regression imputation to produce a synthetic part of the data to allow for an intention to treat analysis that includes all patients. For all analyses on primary and secondary outcomes a *p* value < 0.05 will be considered to indicate statistical significance. However, interpretation of these significant results will primarily focus on clinical relevance.

The primary outcome (percentage responders at 4 weeks) will be computed by using multi-level logistic regression analysis in the MEP study due to its cluster design, and linear regression analysis in the pilocarpine study taking the randomization stratification variable (sex) into account. Results will be expressed as odds ratio (OR) with a 95% confidence interval (CI).

All secondary outcome measures will be described in full using either mean and standard deviation median and interquartile range for continuous measures or count and proportion for categorical measures. Between-group differences in secondary outcomes at 4, 8, and 12 weeks (i.e., mean GOHAI-NL scores [33], mean PRFS scores [35], and patients’ Global Perceived Effect [37] dichotomized into success and no success) will be tested using multivariable generalized linear regression analysis with a link-function depending on the distribution of the variable (i.e. gaussian, or linear regression for continuous variables, binomial, or logistic regression for binary outcomes).

Cost-effectiveness analysis will be performed to examine both the costs and health outcomes of the interventions versus the control group, using the EQ-5D-5L [34], iMCQ [38] and factual costs of the medicine.

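### Cutting the 0-10 NRS to responder yes/no for the MEP primary test costs about 5-12 points of power if the MEP shifts dry mouth scores broadly

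*Protocol article*

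**What the plan says.** Under Primary outcomes, the article sets the endpoint as "percentage responders at week 4, for which a clinically relevant response is defined as at least a 2-point reduction on the 11-point numeric rating scale". Under Analysis of effect evaluation it fixes the MEP test: "The primary outcome (percentage responders at 4 weeks) will be computed by using multi-level logistic regression analysis in the MEP study". No baseline NRS covariate is named for that model.

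The MEP sample size rests on the same binary endpoint. The intervention arm is expected "to have at least 25% more responders" and the calculation is made "with a power of 0.8, an alpha of 0.05 and an intra cluster coefficient of 0.10", giving 181 evaluable patients in 12 clusters and 228 after 20% dropout. The control responder rate is not stated.

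Table 2 shows the NRS recorded at weeks 0, 2, 4, 8 and 12. Secondary outcomes lists, under durability, "changes in mean NRS dry mouth scores in the intervention versus the control group at all time-points".

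**The concern.** The trial records an 11-point score before and after, then tests only whether the drop reaches 2. A fall from 9 to 2 counts the same as a fall from 9 to 7, and a patient who worsens counts the same as one who improves by 1 point. The reason given for the cut is clinical relevance. That is a sound reason to report responders, but it does not oblige the trial to use them as the test variable.

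With six clusters per arm, information is scarce and cannot easily be increased. The scale of the primary test is one of the few things that can still be improved without more patients. The starting score also matters because organisations are allocated first come, first served, so the arms may differ at baseline.

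**Working it through.** **The plan's own figures.** 181 / 0.8 = 226.25, which rounds up to 12 x 19 = 228, so the dropout step reproduces. The 181 cannot be checked outright because the control rate is missing. With m = 181/12 = 15.08 patients per cluster, the design effect is 1 + 14.08 x 0.10 = 2.41. The usual two-sided formula (pooled variance) gives 178 to 183 patients (37 or 38 per arm x 2 x 2.41) at a control rate of about 6-6.5%.

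**Inputs for the comparison.** From Sample size, MEP study: 181 evaluable (90.5 per arm), 12 clusters, ICC 0.10, alpha 0.05. My assumptions: two-sided test; 25% read as an absolute difference; control rate p0 of 20-50%; a normal NRS change that the MEP shifts as a whole.

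**Formulas.** With p1 = p0 + 0.25:
- Shift in SD units: d = probit(p1) - probit(p0).
- Binary test statistic: 0.25 x sqrt(90.5/DE) / sqrt(p0q0 + p1q1).
- NRS test statistic: d x sqrt(90.5/(2 x DE)).
- DE = 1 + 14.08 x ICC, with the ICC belonging to the scale in use.

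Cutting a clustered normal variable lowers its ICC, so the two scales cannot both have 0.10 under this model. I matched them through the bivariate normal, in both directions.

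**Worked case, p0 = 25%, responder ICC 0.10.** d = 0 + 0.674 = 0.674. Binary: 0.25 x sqrt(90.5/2.41)/sqrt(0.1875 + 0.25) = 2.32, power 63.9%. The matching NRS ICC is 0.167, so DE = 3.35 and the NRS statistic is 0.674 x sqrt(90.5/6.70) = 2.48, power 69.8%. The gain is 5.9 points.

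| Control rate | Which ICC is 0.10 | Normal reference: binary to NRS | t reference, 10 df: binary to NRS |
|---|---|---|---|
| 20% | responder | 67.0% to 73.9% (+6.8) | 58.2% to 65.0% (+6.8) |
| 25% or 50% | responder | 63.9% to 69.8% (+5.9) | 55.3% to 61.0% (+5.7) |
| 37.5% | responder | 61.0% to 66.0% (+5.0) | 52.5% to 57.2% (+4.7) |
| 20% | NRS | 79.2% to 87.4% (+8.1) | 70.6% to 79.8% (+9.2) |
| 25% or 50% | NRS | 75.6% to 83.2% (+7.7) | 66.8% to 75.0% (+8.3) |
| 37.5% | NRS | 71.9% to 78.9% (+7.0) | 63.0% to 70.2% (+7.2) |

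Gains are taken before rounding. With a pooled variance in the binary formula, the normal-reference gains are 7.5-9.5 (responder ICC 0.10) and 9.2-10.3 (NRS ICC 0.10).

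**Simulation of a real NRS.** I rounded and bounded the scores to 0-10, took baselines of 5 or more, and compared cluster means with a t-test. Change SDs ran from 2 to 3.8; the 3.8 is the pilocarpine pilot figure, and no MEP value is given. For control rates of 20-50% the gain was about 4-9 points. A separate simulation of integer-rounded change gave about 6-12. These figures compare change scores. Adding week-0 NRS as covariate, with an assumed correlation of 0.3, adds about 1 point.

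**When the broad shift fails.** Let 40% of intervention patients improve by 2.5 points and the rest not at all, with a change SD of 1.2. Responder rates are then about 11% and 38%. At NRS ICC 0.10 the binary test has about 93% power and the NRS test about 86%; at ICC 0.16, about 88% and 77%. Here the cut helps.

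**The case against.** The endpoint is deliberate and coherent. The 2-point drop is defined as the clinically relevant response, the sample size is built on it, and the analysis section says that interpretation will centre on clinical relevance. Mean NRS is already a planned secondary outcome. The trial is registered and recruiting, and in the intervention arm the nurses who deliver the MEP also administer the questionnaires. A change of primary test could therefore look like outcome switching. All of this stands. It limits the point to efficiency and makes the timing of any amendment critical.

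Three stronger readings are tempting, and the documents do not support them.
- *The cut costs around 20 points.* Gains of about 18-22 points appear only if ICC 0.10 is applied to both scales at once, which contradicts the normal-shift model behind the comparison.
- *The cut leaves the trial at 61-67% power instead of 80%.* That range follows from assumed control rates. At a control rate of 6.5% the pooled formula gives 80.1% for the same binary test. The missing control rate is a separate matter.
- *The endpoint is unjustified because no regulator or guideline requires it.* The article cites no such requirement, but it is a condensed account, and an endpoint does not need a mandate to be valid.

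The covariates of the MEP model may likewise be set out in a fuller document. Their absence here is a reason to include baseline NRS in the amended model, not a fault in itself.

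On the other side, the project already thinks on the full scale elsewhere. The pilocarpine study has the same primary outcome, yet its 57 per group matches a comparison of means: 2 x (1.96 + 0.84)^2 x 3.8^2 / 2^2 = 56.7 (unrounded quantiles). The 2-point difference is my inference from the introduction to Sample size.

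**Conclusion.** The point holds as a moderate loss of efficiency. If the MEP shifts NRS scores broadly, testing responders costs about 5-12 points of power. The closed-form and bounded-scale results for control rates of 20-50% mostly fall between 5 and 9, and the top of the range comes from the separate simulation. This rests on 181 evaluable patients in 12 clusters, an absolute 25-point difference, a two-sided 5% test, assumed control rates and ICCs made consistent between the scales. The loss is not guaranteed: it can disappear or reverse when benefit is confined to a subgroup and scores otherwise vary little. The article gives no MEP standard deviation, control rate or change distribution with which to settle that. Nothing in the plan is miscalculated or contradictory on this point.

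**What to change.** By documented amendment and registry update, before any outcome data are examined by arm, base the primary week-4 MEP test on a multi-level linear model. Its outcome is week-4 NRS, with arm and week-0 NRS as fixed effects, organisation as random effect, and degrees of freedom suited to 12 clusters. Report the difference in points with its 95% CI. Keep the percentage with at least a 2-point reduction and its odds ratio, also adjusted for week-0 NRS, as the key clinical-relevance result.

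This needs no new patients or measurements. The costs are real, though. A registered primary test changes after recruitment began. It no longer matches the 25% responder basis of the sample size, nor the primary outcome shared with the pilocarpine study. The headline becomes a mean difference, with the responder percentage beside it. If outcome data have already been examined by arm, leave the registered test in place and report the NRS model as a supporting analysis.

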#### Mouth Education Program (MEP) study

The non-pharmacological study is a cluster non-randomized trial with 228 patients divided over twelve clusters (twelve organisations) in two care settings: a hospital setting with six clusters and a nursing home setting with six clusters. Within each care setting, three clusters will be allocated to the intervention arm on a first come, first serve basis (114 patients), after which three clusters will be allocated to the control arm (114 patients). The intervention, the Mouth Education Program (MEP), will be compared to the control, care as usual (CAU) over a twelve-week period. A cluster non-randomized design was chosen to reduce between-condition contamination and to improve recruitment and logistic processes [23].

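### With 12 clusters and 181 evaluable patients, the MEP study does not deliver both alpha 0.05 and power 0.8 unless the unstated control responder rate is about 4% or lower, or about 71% or higher

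*Protocol article*

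**What the plan says.** The Protocol article (Study design, MEP study) describes patients "divided over twelve clusters (twelve organisations) in two care settings". Three hospitals and three nursing homes go to each arm, so there are six clusters per arm.

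Under Sample size, MEP study, the target is a 25-percentage-point difference in responders at 4 weeks: "with a power of 0.8, an alpha of 0.05 and an intra cluster coefficient of 0.10, we will need to include 181 patients", spread over 12 clusters. It continues: "Taking into account a 20% dropout rate at 4 weeks due to the frailty of our study population, 228 patients are needed", which is 19 per centre. The section gives no control responder rate, sidedness or formula.

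Under Analysis of effect evaluation, the primary MEP outcome is analysed by "multi-level logistic regression analysis in the MEP study due to its cluster design". Significance is judged at p < 0.05, and the result is an odds ratio with a 95% CI. No reference distribution, degrees of freedom or small-sample method is named.

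**The concern.** Every patient in an organisation receives the same arm, so the arm effect is estimated from twelve cluster-level contrasts. Its error has about 10 degrees of freedom (12 clusters minus 2), or 9 if care setting is also a fixed effect. Recruiting more patients per cluster does not change this.

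Alpha and power then pull against each other. A normal reference treats the between-cluster variance as if it were known, so it rejects too often and gives too narrow an interval. A reference that respects the 10 df holds alpha but costs power, and the stated 0.8 has to survive that cost. At stake are the false-positive risk for a programme that the Discussion links to guideline integration, and the real chance of detecting a true 25-point benefit.

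**Working it through.** **Inputs from the article:** 12 clusters, 6 per arm; ICC 0.10; alpha 0.05; power 0.8; difference 0.25; 181 evaluable; 20% dropout; 228 enrolled.

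**Assumptions:** two-sided test; equal cluster sizes; ICC on the proportion scale; control rate p1 varied, since the article gives none; p2 = p1 + 0.25.

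**1. The plan's own figures.** Dropout reproduces: 181/0.8 = 226.25, so 227, rounded up to 12 × 19 = 228.

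The 181 cannot be checked without p1. For n independent patients per arm from the two-proportion formula (pooled variance under the null), a fixed 6 clusters per arm needs m = n(1 − 0.10)/(6 − 0.10n) per cluster, and N = 12m.
- p1 = 6.6%: n = 37.6, N = 181.
- p1 = 10%: n = 43, m = 38.7/1.7 = 22.8, N = 273.
- p1 = 20%: n = 54, m = 48.6/0.6 = 81, N = 972.
- p1 from about 30% to 40%: n = 61-62, above the ceiling 6/0.10 = 60, so no cluster size suffices.

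On this formula, 181 is reached only at p1 of about 6.6% or its mirror image 68.4% (8.4% or 66.6% with unpooled variance).

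**2. Power at 181.** Cluster size is 181/12 = 15.08. The design effect is 1 + 14.08 × 0.10 = 2.408. Effective n per arm is 90.5/2.408 = 37.6. The noncentrality is 0.25/√{[p1(1−p1) + p2(1−p2)]/37.6}. Critical values are 2.228 (10 df) and 2.262 (9 df).

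| Control rate | Noncentrality | z, pooled | z, unpooled | t, 10 df | t, 9 df |
|---|---|---|---|---|---|
| 6.6% | 2.91 | 0.800 | 0.828 | 0.746 | 0.735 |
| 10% | 2.72 | 0.747 | 0.776 | 0.689 | 0.678 |
| 20% | 2.40 | 0.643 | 0.670 | 0.582 | 0.572 |
| 30% | 2.27 | 0.595 | 0.620 | 0.534 | 0.525 |
| 37.5% | 2.24 | 0.585 | 0.610 | 0.525 | 0.515 |

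The table is symmetric about 37.5%, so 65% repeats 10% and 55% repeats 20%. Power on 10 df reaches 0.80 only at p1 ≤ 3.9% or ≥ 71.1%. Simulated power of the multi-level logistic model on 10 df is slightly higher (0.73, 0.62 and 0.56 at 10%, 20% and 30%) but still short. If all 228 were evaluable, the calculated values would be 0.72, 0.62 and 0.57.

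**3. Where the shortfall comes from.** At 20%, the z calculation is already 0.80 − 0.643 = 0.157 short, and the t reference takes a further 0.061. From about 20% to 55%, most of the gap is therefore present under z. At 10% (or 65%) the two parts are about equal: 0.053 and 0.058. Measured against the unpooled z, which shares the variance used for t, the t step is larger, about 0.09.

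**4. Type I error if a z reference is used.** A 1.96 cut-off on a t statistic gives 2·P(T > 1.96) = 0.078 (10 df) or 0.082 (9 df). Simulated null trials (12 clusters of 15, ICC 0.10, maximum-likelihood random-intercept logistic model, 2,500 trials per rate) gave Wald z rejection of 8.4%, 8.0% and 8.2% at responder rates of 20%, 30% and 40%. The likelihood-ratio test gave 7.4%, 6.8% and 6.8%. The 10-df reference gave 5.1-5.3%. A separate set of simulations gave Wald z rejection of 8.6% at 20%, 9.5% at 30% and 6.7% at 10%. At 6.6% (1,500 trials), Wald z rejected in 5.8%, the likelihood-ratio test in 9.0%, and the 10-df reference in 2.5%.

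**The case against.** The strongest objection is that the article condenses a fuller protocol. Naming a multi-level logistic model without its degrees of freedom is normal at this level, and an unseen SAP may specify a small-sample correction. That stands for the type I error. A reader might infer that the plan commits to an uncorrected Wald z test, but the text names no test statistic or reference distribution, so the 8-9% is what would follow from that choice and is not a property of the plan as written.

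The objection does not reach the power. The sample size is a completed calculation in this document, and a SAP with the correct reference would still be left with six clusters per arm.

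It is also fair that nobody can show how 181 was derived. With no control rate, sidedness or formula given, one cannot assert that a small-sample allowance was left out. Nor can one exclude a control rate of about 4% or less, or 71% or more, at which both targets could be met. However, the article gives no figure supporting either extreme.

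**Conclusion.** The point holds in a bounded form. Under a two-sided test with ICC 0.10 and 181 evaluable patients in 12 equal clusters, alpha 0.05 and power 0.8 are not both met at any control rate between about 4% and 71%. A valid between-cluster test has power of about 0.75 at best where the z formula gives 0.80, and about 0.53 to 0.69 at control rates of 10-30%. The excess type I error, about 8-9% at responder rates of 20-40% and nearer 6-7% or less for the Wald test at 10% or below, applies only if no small-sample correction is used.

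Two stronger readings are tempting, and the documents support neither. One is that true power is 70-71% on the plan's own assumptions. That figure belongs to a generic design with exactly 80% power under z (noncentrality 2.80, giving 0.714 on 10 df and 0.704 on 9 df) and uses neither the 181, the ICC nor the 25-point difference. The other is that the reference distribution explains the whole shortfall. Over control rates of 10-65%, the pooled z calculation alone gives only about 0.59 to 0.75, so the unstated control rate is generally the larger issue.

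**What to change.** In Analysis of effect evaluation, or in the SAP if it is not already there, state that the MEP arm effect is tested, and its odds-ratio CI built, on between-cluster degrees of freedom: 10, or 9 if care setting is a fixed effect. An equivalent small-sample correction such as Satterthwaite would also serve. A cluster-level comparison of responder proportions is an optional supporting check.

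In Sample size, MEP study, state the assumed control responder rate, the sidedness and the formula behind 181. Recompute the power with the same reference distribution as the analysis, and report that figure; do not substitute a fixed 70-71%.

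The analysis change costs wording and a software setting, needs no extra patients, and widens the interval slightly. The restated power will be less favourable. Regaining 0.80 would be a separate and larger decision: at 15 evaluable patients per cluster it needs about 8 clusters per arm at a 10% control rate, 10 at 20% and 11 at 30%, against the 6 planned.

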#### Pilocarpine study

The pharmacological study is a four-week double-blind placebo-controlled randomized trial with an eight week unblinded extension treatment period with off-label pilocarpine eye drops with 120 patients from either hospital or nursing home setting. The study intends to evaluate the effect of locally administered oral pilocarpine drops (3 × 5 mg of pilocarpine per day) in reducing complaints of dry mouth in a palliative population at the expense of limited adverse events, as compared to placebo. A double-blind placebo-controlled randomized controlled design was chosen to minimize response bias and achieve a high level of evidence.

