### Study population

#### Patients with dry mouth

In both studies, patients in the palliative phase of their disease with moderate to severe dry mouth symptoms will be invited to participate in the study. Eligibility is assessed using the following inclusion criteria: dry mouth severity ≥ 5 on a scale from 0 to 10 (NRS), a life-limiting condition or frailty [24], an age of 18 years or older and possible palliative care needs as measured by the surprise question [25]. In order to fulfill the surprise question, that is “Would you be surprised if the patient died within 12 months?”, the answer must be “No”. Patients with severe cognitive decline, with previous radiotherapy to the head-neck area and/or with Sjögren’s syndrome will be excluded. Patients with a life expectancy of ≤ 4 weeks will also be excluded due to the primary endpoint being set at 4 weeks. Lastly, in the pilocarpine study patients with mobility impairments impeding correct administration of the drops will be excluded.

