#### Pilocarpine study

Patients will be recruited in two hospitals (one university hospital, one regional hospital) and nursing homes affiliated with The Living Lab in Ageing & Long-Term Care. Recruitment and identification of eligible patients will be carried out by the hospital’s palliative care consultants and nursing homes’ nurses based on the inclusion and exclusion criteria. When an eligible patient has been identified, the care teams will hand over an information letter and the research team will be notified. After a minimum of 1 day, the research team will perform an informative visit to explain the study procedures and the application of the drops, answer any questions and further assess eligibility. After 7 days of deliberation time, formal written informed consent will be obtained. The inclusion procedure will then be followed by (block) randomization of the patient to either pilocarpine or placebo using ALEA®. The randomization outcome will be blinded for both the patient and the researchers. After randomization, the study will officially commence as visualized by Fig. 1.

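### The pilocarpine primary model names sex as its only covariate; adding the week-0 NRS, already collected, is a free but minor gain in precision

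*Protocol article*

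**What the plan says.** All references are to the protocol article.

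- **Entry** (Study population, Patients with dry mouth): patients need "dry mouth severity ≥ 5 on a scale from 0 to 10 (NRS"), so week-0 scores run from 5 to 10.
- **Endpoint** (Primary outcomes): a responder at week 4 has "at least a 2-point reduction on the 11-point numeric rating scale (NRS").
- **Settings** (Study design, Pilocarpine study): the trial takes "120 patients from either hospital or nursing home setting".
- **Randomisation** (Study procedures, Pilocarpine study): inclusion is "followed by (block) randomization of the patient to either pilocarpine or placebo using ALEA". No stratification factor is named there.
- **Primary model** (Data analysis, Analysis of effect evaluation): "linear regression analysis in the pilocarpine study taking the randomization stratification variable (sex) into account", with the result given as an odds ratio and 95% confidence interval. Stratification by sex is mentioned only here.
- **Data available** (Table 2 and Baseline measures): the NRS is taken at week 0 and at every later visit, and care setting is a baseline item.

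**The concern.** The endpoint is computed from the week-0 score, and patients are selected for being at or above a cut-off on that same scale. Regression to the mean is therefore plausible: a patient who enters at 9 or 10 may well drop 2 points on placebo more often than one who enters at 5. If so, week-0 NRS is prognostic for response, and a model without it leaves explainable variation in the residual and does not correct for a chance difference in entry severity between two arms of 60. Sex, the one covariate named, is not linked to response anywhere in the article. What could be lost is some power, and an estimate less exposed to chance imbalance. The false-positive rate is not at risk.

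**Working it through.** **1. The plan's own figure.** Inputs: SD 3.8 (Sample size, Pilocarpine study) and a difference of 2 points (Sample size, opening paragraph). Two-sided alpha 0.05 and power 0.80 are assumed, because for this study the article states neither the sidedness nor the power.

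n per arm = 2 × (1.960 + 0.842)² × 3.8² / 2² = 2 × 7.85 × 14.44 / 4 = 56.7, so 57. This reproduces the stated 57 per group.

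**2. Can every entrant respond?** The lowest admitted score is 5, and 5 - 2 = 3, which is well above 0. The scale floor blocks nobody.

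**3. When does baseline predict response?** Write the expected placebo score at week 4 as 6.2 + slope × (b - 7), where b is the entry score, with a normal residual of SD 2 and rounding to whole points. These values are assumptions; the article gives none of them. Then

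P(response | b) = Φ{[b - 1.5 - 6.2 - slope × (b - 7)] / 2}.

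Example at slope 0.2: b = 5 gives Φ(-2.3/2) = 0.12, and b = 10 gives Φ(1.7/2) = 0.80. At slope 1.0, b cancels and the probability is Φ(-0.35) = 0.36 at every entry score.

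**4. Power and type I error.** Simulation with 60 per arm, 1,500 trials per cell, entry scores 5 to 10 with assumed weights, and logistic regression on treatment without or with week-0 NRS. Sex was left out of both models, which amounts to assuming it is unrelated to response. Response by entry score, correlation and type I error are for residual SD 2 with no drug effect.

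| Slope | Placebo response, entry 5 to 10 | Correlation of week-0 NRS with response | Power without / with (residual SD 2, effect 1.3) | Power without / with (residual SD 3, effect 1.5) | Type I error without / with |
|---|---|---|---|---|---|
| 0.2 | 12% to 80% | 0.41 | 0.697 / 0.747 | 0.541 / 0.551 | 0.054 / 0.047 |
| 0.5 | 20% to 65% | 0.27 | 0.769 / 0.781 | 0.590 / 0.599 | 0.039 / 0.042 |
| 0.8 | 29% to 48% | 0.11 | 0.811 / 0.797 | 0.608 / 0.606 | 0.037 / 0.045 |
| 1.0 | flat, 36% to 37% | 0.00 | 0.806 / 0.796 | 0.612 / 0.603 | 0.059 / 0.059 |

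The change in power runs from about -1 point (at most -1.5) to +5 points. The Monte Carlo standard error of one power figure near 0.8 is √(0.8 × 0.2 / 1500) = 0.010, so the small losses should not be over-read.

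**5. A second set of assumptions.** 57 per arm, scores from a population with mean 6 and SD 2.2, entry at 5 or more. Power without / with week-0 NRS:

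- Retest correlation 0.4: 0.48 / 0.52 (effect 1.0) and 0.72 / 0.76 (effect 1.3).
- Retest correlation 0.6: 0.60 / 0.63 and 0.83 / 0.85.
- Retest correlation 0.8: 0.81 / 0.81 and 0.97 / 0.97.
- With the article's SD of 3.8 taken as the score SD and an effect of 2 points: 0.68 / 0.69 (correlation 0.4) and 0.78 / 0.77 (correlation 0.6).

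**6. Chance imbalance.** The entry scores assumed in step 4 have SD 1.44, so the between-arm difference in mean week-0 NRS has SD 1.44 × √(2/60) = 0.26. In the step 5 setting (SD 2.2), the difference exceeded 0.5 points in about 6 to 9% of trials. Each point of imbalance moved the responder difference by 8 to 11 percentage points at correlations 0.4 to 0.6, and by about 3 at 0.8. Half a point is therefore worth about 4 to 5.5 percentage points, or about 1.5 at correlation 0.8.

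**The case against.** The strongest reply has four parts.

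- **Nothing is invalid.** The trial is randomised, and the model takes its stratification factor into account. Omitting a prognostic covariate does not bias the test, and chance imbalance is already inside its error rate. This stands in full.
- **The article is condensed.** A full analysis plan may list more covariates, and the article does not say that sex is the only one. This limits certainty. But the article does state the primary model and names a covariate, so the point addresses a stated choice. If the full plan already adjusts for week-0 NRS, the point falls away.
- **The benefit is uncertain.** Every input on the baseline-to-week-4 relation is assumed. With the article's own SD of 3.8 and 2-point difference, the gain is essentially nil. This stands: a gain of 3 to 5 points is the upper part of the range, not the expected result.
- **Adjustment changes the estimand.** The adjusted odds ratio is conditional on week-0 NRS. This stands, and reporting both estimates meets it.

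A reader might go further and infer that entry severity largely determines who can achieve a 2-point fall. The article does not support that. Every entrant has room to fall 2 points, and no passage reports how baseline relates to response. In the simulations the correlation runs from 0.41 to 0.00. At the 0.24 to 0.32 found for retest correlations 0.6 and 0.4, week-0 NRS accounts for about 6 to 10% of the variance in response (0.24² to 0.32²).

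A reader might also infer that care setting must enter the model because hospital and nursing home patients are pooled. No passage links setting to response, and no gain was calculated for it.

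**Conclusion.** The point holds as a free improvement of minor severity. The stated pilocarpine primary model leaves out a covariate that is collected from every patient and from which the endpoint itself is calculated. If the week-0 to week-4 slope is below 1, that covariate predicts response, to a degree the article does not give. The sex-only test remains valid. Under the assumed slopes, correlations, SDs and effects, adjustment changes power by about -1 to +5 percentage points and leaves the type I error at about 0.04 to 0.06. The gain is largest when week-4 scores depend weakly on week-0 scores, and vanishes as the slope or retest correlation becomes high.

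The quoted sentence needs revision in any case: it names linear regression for a binary outcome whose result is to be an odds ratio.

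**What to change.** In Analysis of effect evaluation, replace the pilocarpine clause with a statement that response at week 4 is analysed by logistic regression on treatment, sex and week-0 NRS (continuous). Report the treatment odds ratio with its 95% confidence interval, and show the estimate from the model with treatment and sex only beside it. State which of the two is primary, since the first is conditional on week-0 NRS. Care setting may be added but is optional.

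The cost is one sentence. It needs no new data, no more patients and no change to the randomisation. The change should be recorded before unblinding so that the adjusted model counts as prespecified.
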